## Abstract

**Background:**

Depression is a common affliction for young adults, and is associated with a range of adverse outcomes. Cognitive-reminiscence therapy is a brief, structured intervention that has been shown to be highly effective for reducing depressive symptoms, yet to date has not been evaluated in young adult populations. Given its basis in theory-guided reminiscence-based therapy, and incorporation of effective therapeutic techniques drawn from cognitive therapy and problem-solving frameworks, it is hypothesized to be effective in treating depression in this age group.

**Methods and design:**

This article presents the design of a randomized controlled trial implemented in a community-based youth mental health service to compare cognitive-reminiscence therapy with usual care for the treatment of depressive symptoms in young adults. Participants in the cognitive-reminiscence group will receive six sessions of weekly, individual psychotherapy, whilst participants in the usual-care group will receive support from the youth mental health service according to usual procedures. A between-within repeated-measures design will be used to evaluate changes in self-reported outcome measures of depressive symptoms, psychological wellbeing and anxiety across baseline, three weeks into the intervention, post-intervention, one month post-intervention and three months post-intervention. Interviews will also be conducted with participants from the cognitive-reminiscence group to collect information about their experience receiving the intervention, and the process underlying any changes that occur.

**Discussion:**

This study will determine whether a therapeutic approach to depression that has been shown to be effective in older adult populations is also effective for young adults. The expected outcome of this study is the validation of a brief, evidence-based, manualized treatment for young adults with depressive symptoms.

**Trial registration:**

Australian New Zealand Clinical Trials Registry ACTRN12613000084785.

## Background

Depression is a prevalent mood disorder that is one of the leading causes of disability worldwide [1]. Although depression affects individuals across the adult lifespan, onset typically occurs in adolescence or young adulthood [2], with the average age of first episode around 25 years [3,4]. The early onset of depressive symptoms, prior to the age of 25, has also been found to be predictive of a longer duration of symptoms, increased number of depressive episodes and higher frequency of suicide attempts relative to later onset of depression (over 40 years of age) [5]. In Australia, findings from the 2007 National Survey of Mental Health and Wellbeing [6] indicated the 12-month prevalence of major depressive episodes to be 4.1%. However, for individuals aged 16 to 24, this prevalence was higher, at 6.3%. Furthermore, some evidence suggests that this prevalence is increasing [7].

Psychological therapies for depression can provide long-term positive outcomes for sufferers of depression [8,9] and reduce the risk of further episodes [10-12]. However, a substantial number of individuals do not respond to currently available psychological treatments [13], and expert working groups have recommended the continued development or refinement of existing therapies [14]. It is therefore clear that there exists an imperative for the evaluation of new interventions for treating depressive symptoms in young adults.

Reminiscence-based psychotherapies, which utilize the purposeful review and analysis of autobiographical memories as a core component of therapy, have been shown to be an evidence-based treatment approach for attenuating depressive symptoms [15]. An extensive body of research investigating the associations between memory and depression indicates that reminiscence plays an important role in the maintenance of symptoms. Compared with those who are not depressed, clinically depressed individuals remember relatively more emotionally negative events [16] and use a more depressive explanatory style when recalling life narratives [17]. Depressed individuals also exhibit a tendency for overgeneralization when recalling memories, and this can impair their ability to cope with stressors through problem solving and reduce their ability to use memories to predict future events rationally and accurately. Furthermore, it is predictive of more severe depressive symptoms and delayed recovery [18,19].

Meta-analyses of evaluations of reminiscence-based therapies [15,20] have shown significant effects for these approaches in reducing depressive symptoms. Those reminiscence-based therapies that incorporate other therapeutic frameworks for conceptualizing and treating depression have been particularly compelling. Of these, cognitive-reminiscence therapy has demonstrated perhaps the most promising outcomes, with consistently large pre-post-treatment effect sizes [21-23] and high patient-reported satisfaction [23]. Cognitive-reminiscence therapy incorporates structured and guided reminiscence utilizing a Beckian cognitive therapy model of depression treatment [24,25] and a stress and coping model of depression [26,27] with problem-solving techniques [28]. Although this treatment has only been evaluated with older adults, it has been argued that it may also be appropriate and effective in young adult populations [29].

In cognitive-reminiscence therapy, therapists assist individuals in reviewing events and experiences from their life whilst using established therapeutic techniques from the frameworks discussed previously to restructure negative and dysfunctional beliefs, positively reframe and re-story narratives, and build self-efficacy and coping skills. It is proposed that this approach works through several specific mechanisms to treat depression. Firstly, increasing autobiographical memory specificity can disrupt depressed individuals’ tendency to use overgeneral and negatively-valanced memories. Indeed, results from several recent trials have shown that simply eliciting specific autobiographical memories in a concerted manner can decrease depressive symptoms [30,31] and increase problem-solving skills [32]. Secondly, the cognitive therapy techniques employed when reviewing past memories, such as psychological distancing and adaptively restructuring beliefs, have been shown to underpin reductions in depressive symptoms [33,34]. Thirdly, the problem-solving techniques that are used to highlight past coping ability, build a sense of resilience and formulate new solutions to current challenges, have been shown to be effective for treating depression [28], and specifically for young adults [35].

Previous trials of cognitive-reminiscence therapy have examined its effects in a group-based format, typically with two to four individuals [21-23]. Little is currently known though about the effect of this intervention in a one-to-one, individual therapy format. Relative to group therapy, an individual format for treatment would conceivably allow the therapist and client additional time within sessions to examine and reinterpret events and experiences from the past more fully, to form a more positive life narrative. Research generally supports the notion that individual therapy is more effective than group therapy in the treatment of depression [36,37]; however, this premise has yet to be tested in the case of cognitive-reminiscence therapy.

In summary, cognitive-reminiscence therapy has been shown to be a highly effective intervention for depressive symptoms that has not been evaluated with young adults to date. Our trial will aim to rectify this gap in the clinical research literature by implementing a randomized, controlled trial to provide evidence of its effectiveness relative to usual care in a community-based youth mental health service. The trial was designed to address two questions. Firstly, is cognitive-reminiscence therapy effective in reducing depressive symptoms in young adults? And secondly, how effective is cognitive-reminiscence therapy in comparison with usual care at a youth mental health service?

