## Methods and design

### Study design

To evaluate the effectiveness of cognitive-reminiscence therapy in the treatment of young adults with depressive symptoms, we will conduct a randomized controlled trial and compare this intervention with usual care. We will utilize a between-within, repeated-measures design over five time-points (baseline, three weeks into the intervention, post-intervention, one month post-intervention, and three months post-intervention) to assess for both within-group change and differences between these groups in change.

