### Participants

Young adults will be recruited from a community youth mental health service in the city of Melbourne, Australia. As the eligible age of intake at these participating services is capped at 25 years of age, it is not anticipated that any individuals will exceed this age range. The inclusion and exclusion criteria for participation will be:

1. 18 years of age, or older.

2. The presence of at least moderate depressive symptoms, as indicated by a score of seven or higher on the DASS-21 depression subscale [38].

3. Not currently receiving any other treatment for depression.

4. Depressive symptoms are not the product of physical causes (for example, hypothyroidism).

5. Not at high risk of suicide or harm to others (as assessed through intake interviews).

6. Not presenting with a primary problem related to psychotic symptoms, disordered eating, manic symptoms, body image disturbance, anxiety, substance use or sexual dysfunction.

Individuals will only be excluded from participating in the study in the case that problems other than depression are the primary reason for presentation (as assessed at intake), or other problems emerge as the primary reason for help-seeking during treatment and therefore supersede depressive symptoms as the likely target for therapy (as assessed during the course of the study).

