### Sample size

Sample size was calculated using GPower 3 [42], with two aims of the current study under consideration: whether participants in the cognitive-reminiscence therapy group report improvements on measures over time, and whether these effects differ from those achieved by usual care. Although previous evaluations of this intervention with older adults have produced large effect sizes; [21-23], it was decided to err on a somewhat more conservative side and estimate a sample size for a moderate-to-large within-group effect over time. It was calculated that using a repeated-measures within-subject analysis of variance (ANOVA) across five time-points with an α level set at 0.05 (two-tailed), statistical power level (1 − β) of 0.80, and an estimate of correlation among repeated measures of 0.5, 15 participants will be needed in the cognitive-reminiscence group to detect this effect. To assess for a small-to-moderate interaction effect between groups and time using the parameters described above, a total of 32 participants (16 per group) will be needed. After factoring in the average dropout rate of 20% for reminiscence-based therapies [20], it is estimated that a minimum of 19 participants per group (total *N* = 38) will need to be recruited to assess within-group effects and differences between groups in treatment effects.

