Despite the new findings that this trial is likely to generate, several limitations may be forecast. Perhaps most importantly, the small sample size of this trial is likely to limit the generalizability of the findings, and to limit the opportunity to identify moderating variables. However, as no pilot studies in this age group exist, and therefore the effectiveness of this therapy with young adults is largely unknown, a larger trial and the resources necessary to conduct it could not be justified at this stage. Depending on the outcomes of this trial, future research may look to utilize a larger sample. There is a chance that young adults will not respond well to this retrospectively oriented treatment modality, although no reliable evidence currently exists to support this contention, and a reasoned argument to the contrary has been constructed based on developmental and cognitive-based research [29].

In summary, the expected outcomes of this study are the validation of a manualized, therapeutic approach to treatment of depression in young adults, and new data concerning young adults’ experience of receiving this intervention and changes relating to broader psychological wellbeing that may occur. This manualized psychotherapy may then be implemented in mental health services to address the needs of young adults presenting with depressive symptoms.

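### Question 1 (is the therapy effective?) is tied to change over time in the therapy arm alone, which cannot separate a treatment effect from natural recovery; the plan should rest effectiveness on the randomised contrast only

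*Protocol article*

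**What the plan says.** The last paragraph of the Background poses two questions. The first is "Firstly, is cognitive-reminiscence therapy effective in reducing depressive symptoms in young adults". The second is "And secondly, how effective is cognitive-reminiscence therapy in comparison with usual care at a youth mental health service". The Sample size section restates them as two aims: "whether participants in the cognitive-reminiscence therapy group report improvements on measures over time, and whether these effects differ from those achieved by usual care". It sizes the first aim by choosing to "estimate a sample size for a moderate-to-large within-group effect over time", using a within-subject ANOVA over five time-points (α 0.05, power 0.80, correlation 0.5), which gives 15 participants in the therapy group. The second aim has its own calculation for a group-by-time interaction, which gives 32 in total. Study design says that the repeated-measures design is meant "to assess for both within-group change and differences between these groups in change".

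Four other places bear on the point:
- Under Participants, entry requires at least moderate symptoms, "as indicated by a score of seven or higher on the DASS-21 depression subscale". The same subscale is the primary outcome.
- Under Conditions, therapy participants may use any other support after the sixth session.
- Usual care is expected to be evidence-based psychological treatment, so the comparator is active.
- The Discussion closes by saying that "the expected outcomes of this study are the validation of a manualized, therapeutic approach to treatment of depression in young adults".

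The Analysis section plans repeated-measures ANOVAs, Cohen's d with 95% confidence intervals and a reliable change index. It does not say which contrast decides whether the therapy is effective.

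**The concern.** A fall in mean score within one arm is the sum of any treatment effect, the natural course of depression in people who have just sought help, and, once the six sessions are over, any other support they take up. A one-group time effect cannot separate these. Because the first aim has its own question, test and sample size, a reader of the results could treat a significant time effect in the therapy arm as a positive answer to Question 1, whatever the randomised comparison shows.

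That combination is plausible. The comparator is active, and the interaction test is sized for a large sustained difference between arms (see the working). If a significant time effect came with a non-significant interaction, the aims as worded would let the trial answer yes to Question 1 although the randomised evidence had shown no difference.

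**Working it through.** **Inputs from the Sample size section.** Five time-points (m = 5), α = 0.05, power 0.80, correlation ρ = 0.5, n = 15 for the one-group test, N = 32 for the interaction, 19 per group to be recruited. The effect sizes are given only in words, so f is back-solved.

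**Step 1: reproduce the plan's figures.** Noncentral F, sphericity assumed.
- One group: λ = f²·n·m/(1−ρ), df = (m−1) and (n−1)(m−1). With f = 0.30 and n = 15, λ = 0.09 × 15 × 5/0.5 = 13.5, df = 4 and 56, power 0.817. At n = 14 power is 0.783, so 15 is the smallest n.
- Interaction: λ = f²·N·m/(1−ρ), df = (m−1) and (N−2)(m−1). With f = 0.20 and N = 32, λ = 0.04 × 32 × 5/0.5 = 12.8, df = 4 and 120, power 0.814.

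Both stated sizes reproduce.

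**Step 2: what f = 0.30 means.** Take a fall of d SD that is present at the second time-point and sustained, i.e. means (0, d, d, d, d). The mean shift is 0.8d, and the SD of the five means is d·√(0.2 × 0.8² + 0.8 × 0.2²) = 0.4d. So f = 0.4d, and f = 0.30 is a sustained fall of 0.75 SD from any cause.

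**Step 3: rejection rate of the one-group test when the treatment effect is zero.** Put an uncontrolled fall d into f = 0.4d. The documents give no recovery rate, so the values of d are assumptions.

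| Uncontrolled fall | f | n = 15 | n = 19 |
|---|---|---|---|
| 0.3 SD | 0.12 | 17% | 21% |
| 0.5 SD | 0.20 | 43% | 55% |
| 0.75 SD | 0.30 | 82% | 91% |

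Simulation with selection at a score of 7 or more and a separately measured baseline (assumed SD 5, service mean 9) agrees: 17% and 21% at 0.3 SD, 44% and 54% at 0.5 SD.

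**Step 4: the randomised test under the same conditions.** With 16 per group, no treatment difference, selection on the scale and either no recovery or a 0.5 SD recovery common to both arms, the simulated group-by-time test rejected in 4.5% to 5.3% of trials. A change shared by both arms cancels.

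**Step 5: size of the interaction effect.** A difference of δ SD between arms at all four later time-points puts each arm δ/2 from the common course, so f = 0.4 × δ/2 = 0.2δ. Thus f = 0.20 is δ = 1.0 SD. At δ = 0.5, f = 0.10, λ = 0.01 × 32 × 5/0.5 = 3.2 and power is 25%.

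**Step 6: regression to the mean, if the screening score served as baseline.** Expected fall = (1−r) × (mean of scores at or above 7 − unselected mean), on a normal model. Assumed: unselected mean 6 to 10, SD 4.5 to 5.5, retest correlation r 0.6 to 0.8. The smallest result is 0.38 points (mean 10, SD 4.5, r 0.8; 0.38/4.5 = 0.09 SD). The largest fall in points is 2.0 (mean 6, SD 5.5, r 0.6; 0.37 SD), and the largest in SD is 0.38 (mean 6, SD 4.5, r 0.6; 1.7 points). So the range is about 0.1 to 0.4 unselected SD. If baseline is re-measured after screening, simulation with a constant correlation of 0.5 leaves the one-group test at about 5%. If correlation decays with time, it rejects in 9% to 26% (n = 15 or 19, service mean 7 to 11).

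**The case against.** The strongest reply is that the plan never says a within-arm time effect will count as proof. The Background also says the trial is to give evidence of effectiveness relative to usual care, and Study design says effectiveness will be evaluated by randomising and comparing. The first aim in the Sample size section is worded as reported improvement, not causation. The Analysis section sets no success criterion. The randomised contrast is planned, and it drives the sample size, since 16 per group exceeds 15. All of this stands. A reader might infer that a time effect with a null interaction is to be declared effectiveness, but no section says so. Nor is the validation forecast in the Discussion linked to the within-group test, and that section concedes that the sample is small and effectiveness in this age group largely unknown.

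The reply is also strong on regression to the mean. Because entry and outcome use the same subscale, a reader might infer that regression alone would make the test reject most of the time. The documents do not support this. Procedure places the screen at triage, before consent, and Outcome measures says all measures, including baseline, are completed online through emailed links. That suggests a separate baseline, which would remove much of the effect.

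Finally, the rates in Step 3 are conditional on assumed falls, so the actual error rate is unknown, and a null interaction is plausible but not shown to be likely.

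What the reply does not remove is the separate first question, its one-group test and its own sample size. Nothing labels within-arm change as descriptive, and the limitations mention neither natural recovery nor regression to the mean.

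**Conclusion.** The point holds as an inference that the stated aims leave open. Question 1 is tied to a one-arm test that cannot support a statement about effectiveness. With no treatment effect, it is significant in about 17% to 82% of trials at n = 15, and 21% to 91% at n = 19, for assumed uncontrolled falls of 0.3 to 0.75 SD; the randomised test stays near 5%. These figures assume a fall sustained from the second time-point, correlation 0.5 and sphericity, with f back-solved from the stated sample sizes. Natural recovery alone is enough to carry the conclusion, and regression to the mean is a secondary contribution that matters mainly if the screening score is used as baseline. Because usual care is itself active treatment, the design can answer effectiveness relative to usual care, but not effectiveness in the absolute sense of Question 1.

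**What to change.** Four changes of wording, in Background, Study design, Sample size and Analysis:

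1. Name the randomised group-by-time contrast on DASS-21 depression as the sole basis for any conclusion about effectiveness.
2. Recast Question 1 as descriptive: report change from baseline with 95% CI in both arms. Within-arm p-values need not be banned, provided that they are labelled as not bearing on effectiveness.
3. State that a non-significant between-group result will be reported with its CI and not read as equivalence or as validation of the therapy.
4. State that baseline is measured separately from the screening score, if that is the intention.

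The interaction is already sized at 32 in total, so no new sample size or data collection is needed. The cost is a less favourable set of claims if the arms improve alike.

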## Methods and design

### Study design

To evaluate the effectiveness of cognitive-reminiscence therapy in the treatment of young adults with depressive symptoms, we will conduct a randomized controlled trial and compare this intervention with usual care. We will utilize a between-within, repeated-measures design over five time-points (baseline, three weeks into the intervention, post-intervention, one month post-intervention, and three months post-intervention) to assess for both within-group change and differences between these groups in change.

### Participants

Young adults will be recruited from a community youth mental health service in the city of Melbourne, Australia. As the eligible age of intake at these participating services is capped at 25 years of age, it is not anticipated that any individuals will exceed this age range. The inclusion and exclusion criteria for participation will be:

1. 18 years of age, or older.

2. The presence of at least moderate depressive symptoms, as indicated by a score of seven or higher on the DASS-21 depression subscale [38].

3. Not currently receiving any other treatment for depression.

4. Depressive symptoms are not the product of physical causes (for example, hypothyroidism).

5. Not at high risk of suicide or harm to others (as assessed through intake interviews).

6. Not presenting with a primary problem related to psychotic symptoms, disordered eating, manic symptoms, body image disturbance, anxiety, substance use or sexual dysfunction.

Individuals will only be excluded from participating in the study in the case that problems other than depression are the primary reason for presentation (as assessed at intake), or other problems emerge as the primary reason for help-seeking during treatment and therefore supersede depressive symptoms as the likely target for therapy (as assessed during the course of the study).

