### Procedure

Initially, intake clinicians working at the youth mental services will identify individuals eligible to participate in the study through assessments conducted as part of their normal triage protocol. This includes a structured face-to-face assessment of psychosocial and mental health problems, which provides the information necessary to determine eligibility based on the criteria listed [39]. The study will be introduced to eligible individuals, who will then be screened for the presence of at least moderate depressive symptoms using the DASS-21 depression subscale [38] and provided with the plain language statement. Permission for a member of the research team to contact them will be sought. A member of the research team will then contact them to discuss the details of the study further and answer any questions they may have. If the individuals agree to participate, informed consent will be sought and participants will be randomized into one of the treatment conditions.

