The intervention will be administered on the premises of the participating youth mental health service. The intervention comprises six 60-minute weekly sessions of individual psychotherapy. Over the course of therapy, six different topics are used to stimulate memories as a basis for therapeutic work. These are: turning points, family life, major life works, loves and hates, stressful experiences, and meaning in life. In the first session, rapport is built and psychoeducation is provided on autobiographical memory (specifically, integrative and instrumental types of reminiscence), related depressogenic patterns, and cognitive therapy and stress and coping models of depression. Information is provided about the intervention, including evidence for its effectiveness and what it entails for the participant and therapist. Following this, the first topic, turning points, is discussed, using a list of questions to help stimulate memories. The procedure for therapeutic work then follows the same pattern in each session. Memories are elicited and among these several are identified by the therapist and participant collaboratively as being of importance and to be discussed. The therapist ensures that there is at least one event or experience that is likely to benefit from cognitive therapy techniques and one that relates to stress and coping. These memories are then elaborated on, with the therapist ensuring that sufficient details of the memories are provided so as to promote increases in memory specificity. The respective therapeutic techniques are then utilized where appropriate, for example, restructuring beliefs about perceived failures and negative experiences, focusing on positive experiences and achievements to enhance perceptions of self-worth or self-efficacy, and breaking down previous coping step-by-step and highlighting effective strategies. As a general guideline, the therapist aims to help the individual create a cohesive and positive narrative of their life and a view of themselves that realistically integrates good and bad experiences. Further, therapists orient themselves towards improving clients’ perceptions of their meaning in life, self-esteem, self-efficacy, and optimism, given that these variables have been shown to mediate adaptive reminiscence functions and depressive symptoms [43] and changes produced by reminiscence-based therapies [44,45]. In the first session, a brief problem-solving framework is introduced, and a problem list is elicited for work in subsequent sessions. At the end of the session, a summary is provided and feedback is elicited from the participant on what was learned and any changes that have occurred. A homework sheet is then provided, listing questions related to the next week’s topic. A rationale is provided for this homework sheet, including its usefulness in promoting effective change [46]. The following five sessions follow a similar procedure of reviewing homework on the topic for the week, identifying memories to elaborate on and engaging in therapeutic work with these memories, and utilizing a problem-solving framework to choose solutions to identified problems to implement over the next week. Specific coping strategies that have been discussed in the session are drawn on to assist in the problem-solving work, as well as content related to self-efficacy and approach-coping behaviour that is broadly promoted over the sessions. In the last session, a summary is provided by the therapist of the work completed over the intervention, and the participant is invited to provide feedback of the experience and reflect on any change that has occurred.

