#### Usual care

Participants in the usual-care condition will receive support following the normal procedures implemented by the clinical pathway coordinator of the participating youth mental health service. There will be no restriction on the type, amount or length of support that is received. Given the service in which the study will be conducted, this support will probably consist of six to ten sessions of evidence-based psychological treatment provided by registered mental health professionals. Information will be collected for each participant on what their usual care constitutes so that it can be described as a group and contrasted with the cognitive-reminiscence group. Following the cessation of data collection, all participants in the usual-care group will be invited to receive the six-week course of cognitive-reminiscence therapy should they wish.

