#### Analysis

Baseline characteristics (demographic, clinical and wellbeing variables) will be compared using chi-square analyses for categorical variables and *t* tests for continuous variables. For the primary and secondary outcomes, repeated-measures ANOVAs will be conducted, along with appropriate post-hoc analyses. Effect sizes will be calculated using Cohen’s *d*, which is based on the pooled standard deviation, along with 95% confidence intervals. To assess individuals for clinically significant change on the primary outcome and distinguish between improved, unchanged and deteriorated cases, the reliable change index will be used [58]. Analyses will be conducted on post-treatment data using intention-to-treat methods presented in the CONSORT guidelines [59], with appropriate imputation of missing data. Qualitative data will be analyzed using applied thematic analysis techniques [60]. Interviews will be transcribed, coded and grouped into themes using an iterative process, and then the themes will be refined and interpreted. Quantitative data reduction techniques will also be used to analyze the frequency of particular attitudes and agreement or disagreement with specific questions, such as whether participants thought the intervention was long enough.

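### The protocol excludes participants from the study on a judgement made after randomisation, which on its plain wording conflicts with its intention-to-treat analysis

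*Protocol article*

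**What the plan says.** All references are to the protocol article.

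- **Participants.** The paragraph after the numbered criteria gives two grounds for exclusion. The first is judged at intake: "Individuals will only be excluded from participating in the study in the case that problems other than depression are the primary reason for presentation". The second applies when "other problems emerge as the primary reason for help-seeking during treatment and therefore supersede depressive symptoms as the likely target for therapy", and its timing is given as "as assessed during the course of the study". In both cases the person leaves the study, not only the therapy.
- **Procedure.** After screening and discussion, "informed consent will be sought and participants will be randomized into one of the treatment conditions". Treatment follows.
- **Analysis.** The analyses are to be done "using intention-to-treat methods presented in the CONSORT guidelines [59], with appropriate imputation of missing data".
- **Cognitive-reminiscence.** "The intervention comprises six 60-minute weekly sessions of individual psychotherapy", based on a manual, with a therapist checklist of required components after each session.
- **Usual care.** "There will be no restriction on the type, amount or length of support that is received".

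The article does not say who makes the second judgement, by what rule, or whether it is made the same way in both arms. Nor does it say that a person excluded on this ground continues to receive questionnaires or is analysed.

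**The concern.** Intention-to-treat keeps every randomised participant in the comparison, in the arm assigned, whatever happens later. A rule that takes people out of the study because of something that emerges during treatment works against this.

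Two features make it more than a formality. First, the trigger is that another problem has overtaken depression as the focus of therapy. That can depend on how the depression itself is going, and depression is the primary outcome. Second, the arms differ in how such a change would show. One has weekly sessions of a manualised depression therapy, where a change of target is easily seen and may not fit the manual. The other may change its content freely. If removal is related to outcome and unequal between arms, the arms that remain are no longer comparable.

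There is also a practical loss. Outcomes are self-reported through emailed links, so they can be collected from someone who has stopped the therapy. Outcomes that were never requested cannot be recovered by a later analysis plan.

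**Working it through.** **1. Order of events.** The first ground is assessed at intake, before consent and randomisation, and raises no difficulty. The second is assessed during treatment. Randomisation precedes treatment, so the second ground acts only on people already randomised.

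**2. Participants against Analysis.** There are two ways to read them together.
- *Excluded from the study means no more data and no place in the analysis.* The analysis set is then not all randomised participants, and the intention-to-treat commitment is not met.
- *Excluded from the study means no more data, with later values imputed.* Every randomised person is then formally counted. For those removed, however, post-exclusion outcomes rest on an imputation model although they could have been observed, and the reason they are missing may be related to their values.

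The article does not say which reading applies. Neither gives what the Analysis section appears to intend.

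**3. Size, as an illustration.** The plan gives no figure for the number, direction or arm of such exclusions, so there is none to reproduce. The only input from the plan is 19 per group (Sample size). The rest is assumption: *k* people are left out of the analysis in one arm only, and they average *d* SD worse than that whole arm.

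If the whole-arm mean is 0, those removed have mean *d* on the worse side. The 19 − *k* who remain must balance them, so

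shift in arm mean = *k* × *d* / (19 − *k*).

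| *k* | *d* (SD) | Calculation | Shift (SD) |
|---|---|---|---|
| 1 | 0.5 | 1 × 0.5 / 18 | 0.03 |
| 2 | 1.0 | 2 × 1.0 / 17 | 0.12 |
| 3 | 1.5 | 3 × 1.5 / 16 | 0.28 |

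The between-arm difference moves by the same amount if the other arm loses nobody. If those removed were better than their arm by *d*, the shift has the same size and the opposite sign. If both arms lost the same number with the same *d*, the shifts would cancel.

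The last row is at the extreme. Under normality the three worst of 19 average about 1.44 SD below the arm mean, which gives 3 × 1.44 / 16 = 0.27 SD.

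**4. Check by simulation.** Setting: 19 per arm, no true effect, one normal endpoint with SD 1, two-sided *t* test at 5%, 40,000 replicates, exclusions in the cognitive-reminiscence arm only. This is simpler than the planned repeated-measures ANOVA and serves only to show scale.

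| Number left out | Worst outcomes: spurious benefit (SD) | Type I error | Random from worse half: spurious benefit (SD) | Type I error |
|---|---|---|---|---|
| 0 | 0.00 | 5.0% | – | – |
| 1 | 0.10 | 7.0% | 0.05 | 5.1% |
| 2 | 0.19 | 10.3% | 0.10 | 5.7% |
| 3 | 0.27 | 14.7% | 0.15 | 6.9% |
| 4 | 0.35 | 20.3% | 0.22 | 8.8% |

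The value for the three worst agrees with the 0.27 in step 3.

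**The case against.** The strongest reply is that being excluded from participation is not being excluded from analysis. The phrase stands among criteria for participation, and the Analysis section provides for imputation. On that reading both sections can be followed, so a reader who infers that they are strictly incompatible goes too far. This stands. What remains is that the article does not choose this reading, and that imputing obtainable outcomes is a poor substitute for collecting them.

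A reader might also infer that the rule removes people from the therapy arm only. The text does not support that. The rule speaks of individuals in general and on its face covers usual care too. Nor does a new problem have to end participation in the therapy arm, since the sessions include a problem list and problem-solving work. Unequal operation is a possibility suggested by the different content of the arms, and no more.

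A third tempting reading is that the rule removes poor responders and so favours the new therapy. The trigger is a change in the main problem, not a lack of response. Depression may be overtaken because it has improved, in which case good responders would go and the bias would run against the therapy. Nor can one say that the judgement is unblinded, since the article does not describe how it is made.

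Finally, the 20% dropout allowance in Sample size may or may not already cover such exclusions. The article does not say, so they cannot be counted as an additional loss.

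That the article is condensed does not answer the point, which concerns a rule the article states, not a detail it leaves out.

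**Conclusion.** The point holds as a conflict between two stated rules. The Participants section removes people from the study on a judgement made after randomisation. The Analysis section promises intention-to-treat. Nothing in the article keeps those people in follow-up or in the analysis.

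Bias is possible, because the exclusion may be related to outcome and may differ between arms. Its direction and size cannot be derived from the document. The shifts of about 0.03 to 0.28 SD rest on four assumptions that the article does not state: one to three exclusions of 19, all in one arm, all in the worse direction, and no imputation. They show that a few removals can matter in a trial of this size. They are not an estimate of what will happen.

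**What to change.** Reconcile the Participants and Analysis sections with a short amendment:

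1. State that having another primary problem is a ground for exclusion only before randomisation.
2. If another problem becomes primary after randomisation, record the date and the reason, in the same way in both arms.
3. Keep sending that participant the online questionnaires at all remaining time-points, unless consent is withdrawn.
4. Analyse every randomised participant in the arm assigned, and keep imputation for outcomes that could not be obtained.
5. Add a sensitivity analysis without the participants recorded under item 2, and report their number by arm.

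The care these participants receive is left to the service and is not part of this change.

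The cost is an amendment of a few sentences and a few more emailed questionnaires. The downside is some dilution of the estimated effect, because the analysis will include people who did not complete the course.
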